## PROTOCOL SUMMARY FOR NEW AND CONTINUING PROTOCOLS

### 1. Provide a brief (200-250 word) summary of the background or statement of the problem.

As the American workforce ages, workplace-based risk reduction strategies that have been shown effective for the broad mainstream of workers offer particular promise for improving the health of older workers (ages 50 and older). With the aging of the baby boom generation, older workers comprise an expanding proportion of the workforce, now about one-third of the workforce, or approximately 50 million workers. Compared to younger workers, this group is at relatively high risk of chronic, debilitating diseases and costly health care services (NRC, 2004, Vita et al., 1998). Moreover, a significant percentage of these chronic diseases are preventable through the application of health promotion practices (Pelletier, 2005). Consequently, it seems likely that the application of health promotion interventions to this older group of workers can help delay the onset of aging and chronic disease, achieving health improvements and cost reductions in this segment of the population. In recent years, computer-based approaches to workplace health promotion and disease prevention strategies have become more numerous, and research has shown that tailored, media-rich web-based programs can improve worker health (Wantland et al., 2004; Rothert et al., 2006; Cook et al., 2007; Billings et al., 2008).

### 2. State purpose of study:

The overall goal of this project is to develop and test a comprehensive, interactive, and innovative web-based program designed to improve the health of older workers. This program will address a wide variety of health behavior topics, including physical activity, nutrition/weight management, stress management, mood management, alcohol use, and tobacco use – the health behaviors that contribute to the likelihood of contracting major diseases. The program will be tested with working adults 50 years of age and older.

### 3. Indicate the total number of subjects and the number of sites:

Number of subjects 300

Number of sites: 1

### 4. Indicate the characteristics of study population:

(a) Gender: Males yes X no \_\_\_\_\_  
Females yes X no \_\_\_\_\_  
(b) Age range: from 50 to 80  
(c) Racial and Ethnic Groups:  
Caucasian yes X no \_\_\_\_\_  
Black yes X no \_\_\_\_\_  
Hispanic yes X no \_\_\_\_\_  
American Indian yes \_\_\_\_\_ no X  
Alaskan Native yes \_\_\_\_\_ no X  
Asian/Pacific Islander yes X no \_\_\_\_\_  
Other (specify) \_\_\_\_\_

#### (d) Justify any exclusion of specific gender, age, and racial or ethnic groups:

The program specifically focuses on changing the health behaviors of people 50 years of age and as such, the 300 participants will be at least 50 years of age. The program is not designed for those under the age of 50.

We have not specifically excluded Alaskan Natives or American Indians. However, their base rates in the EMC employee population are quite low so we do not

anticipate that they will sign up for the study. Should any American Indian or Alaskan Native EMC employee choose to participate, they will be included in the study.

5. State inclusion criteria for enrollment in study:

All EMC employees 50 years of age and older will be recruited to participate in the field test of the employee program.

6. State exclusion criteria for enrollment in study:

The exclusion criteria will be age less than 50.

7. Will vulnerable subjects be enrolled in this study?

(a) Individuals with diminished mental capacity

yes\_\_\_\_\_ no X

(b) children

yes\_\_\_\_\_ no X

(c) pregnant women

yes\_\_\_\_\_ no X

(d) fetuses

yes\_\_\_\_\_ no X

(e) economically or educationally disadvantaged persons

yes\_\_\_\_\_ no X

(f) prisoners

yes\_\_\_\_\_ no X

8. If vulnerable subjects are to be enrolled, describe the special precautions that will be taken to ensure that consent is freely given and that the rights and welfare of the subjects are protected:

N/A

9. If the study involves children, will a Certification of Assent form be used to document that assent was freely given without coercion? yes\_\_\_\_\_ no\_\_\_\_\_

If no, indicate how assent will be documented:

N/A

10. Indicate where and how research data will be stored to ensure confidentiality:

The data will be obtained using a secure password protected online survey tool. The data will be stored in password protected computers and no names will be stored with the data.

Will data (e.g. records, samples, specimens, databases, surveys, etc.) be obtained with identifiers that can be directly or indirectly linked back to the subjects?

yes X no\_\_\_\_\_

There will be a separate file that links the Study ID to the individual. The study ID only, however, will be used in the database with the survey data.

12. Indicate who will have access to information about the subjects that is identifiable:

Member of the study team, not EMC, will have access to the data on a password-protected computer.

13. Indicate how potential subjects will be identified and recruited for participation in the study:

A flyer/email will be sent in a targeted email to all employees fifty years of age and older. EMC will send the flyer/email, not ISA. The flyer/email will indicate that the study is focusing on employees 50 years of age and older. Interested employees who fit the inclusion criteria (age 50 and older) will be asked to contact ISA at the study e-mail or telephone number. Even

though the flyer will be sent specifically to employees 50 years of age and older, the Project Manager will confirm the age at that time employees contact ISA.

When an employee contacts ISA, they will be provided with additional information about the project (see attached summary of what employees will be told when they contact ISA). The Project Manager will address any questions employees have and will then ask two questions to ensure that the employee qualifies for the study (age and whether they are an EMC employee).

14. Indicate when and where consent will be obtained:

Consent will be obtained as part of the first survey data collection. It will be imbedded into the online survey and participants will not be able to continue with the survey until they have acknowledged and indicated that they consent.

15. Indicate how you will determine whether the subjects (or their surrogates) understand the information that was provided in the consent document:

Participants will be asked to indicate on the consent document that they understood the information on the consent form. The telephone number for the project manager and IRB chair will be included if the participant has questions. A hard copy of the consent document will be e-mailed to participants.

16. Summarize, in a narrative what actually will be done to the subjects during their participation in the study. Make certain that the following are included:

- (a) a clear description of what is being done for research purposes and what is being done as part of standard clinical care;
- (b) a list of tests and procedures that will be performed for research purposes (e.g. blood tests, urine tests, cultures, interviews, questionnaires, surgical procedures, cardiac catheterization, pulmonary function tests, X-rays, scans, etc);
- (c) a brief description of the analyses that will be performed on the biologic or non-biologic (i.e. questionnaires) samples collected;
- (d) a list of investigational devices that will be used, indicate if they are classified as significant risk (SR) or non-significant risk (NSR) devices and whether there is an IDE or there is an application to the FDA for an IDE if the device is SR;
- (e) a statement that defines who will be financially responsible for the costs associated with participation in the study (e.g. examinations, procedures, drugs, devices, etc.) and a statement that defines what will be provided without cost to the subjects;
- (f) your assessment of whether the research involves any physical, psychological, social and/or economic risk(s) and the magnitude of the risk(s);
- (g) your assessment of the risk/benefit ratio of the research

NOTE:

a) Data and patient safety monitoring: if required, a Data and Safety Monitoring Board (DSMB), which must be convened by the PI, can be made up of internal and/or external members who have the appropriate expertise and are totally independent of and unaffiliated with the study. The composition of the DSMB should be commensurate with the complexity of the proposed study and will be reviewed by the IRB. Approval of the DSMB by the IRB is required prior to initiating the clinical trial.

## **Narrative:**

(A) a clear description of what is being done for research purposes and what is being done as part of standard clinical care;

All EMC employees age 50 or older will be invited to participate in the field test of the program, approximately 300 of who are expected participate. ISA will then randomly assign 150 employees to the experimental condition and 150 employees to the control condition. Participation will be completely voluntary and employees will be recruited using a promotional campaign as well as monetary incentives (\$25 per data collection) and cash drawing (\$500).

All participants will be asked to complete the self-administered health questionnaire. The survey will be completed on-line through Survey Monkey. All data collected will be done for research purposes. Identification numbers will be used to link pretest and posttest surveys. Upon completion of the pretest data collection, participants will be randomly assigned to the experimental or control conditions. Participants in the experimental condition will be sent information on how to access the *HealthyPast50* program using a randomly generated unique identification number. Participants assigned to the program intervention will be encouraged to view the contents over multiple sessions during the three-month administration period. Employees will be encouraged to use the program during breaks and when not working. This method works best for facilitating optimal learning and helps to alleviate concerns that the worksite may have about time away from the job. Control group participants will be told that they will receive access to the *HealthPast50* program after the second survey. All participants will be allowed to access the EMC health programs as usual.

Approximately three months after experimental group participants receive initial access to the program they will be instructed that program viewing period is over. At that point all, participants will be sent information on how to complete the posttest questionnaire. That data collection will be conducted in a manner similar to the pretest, and as indicated above, once the posttest is complete, control group participants will be given access to the web-based program.

(B) a list of tests and procedures that will be performed for research purposes (e.g. blood tests, urine tests, cultures, interviews, questionnaires, surgical procedures, cardiac catheterization, pulmonary function tests, X-rays, scans, etc);

## **Outcome Measures**

A draft copy of the survey questionnaire is attached. Most of the measures will be self-report scales of health behaviors that the ISA research team has used in several research projects during the past decade (e.g., Cook et al., 1996a, 1996b, 2004, 2005, 2007; Deitz et al., 2005; Billings et al., 2008)) and will therefore have the typically desired psychometric underpinnings -- established reliability coefficients, validity estimates, etc. -- as described below. In addition, several of the scales were developed and validated by other investigators -- e.g., Block et al., 1986; Schwarzer and Renner, 2000; Glynn and Ruderman, 1986 -- but have demonstrated evidence of reliability and validity. For all scales, however, psychometric analyses will be conducted on the measures once the data are in order to ensure that the collection of items can be legitimately summated; e.g., whether they have high Alpha coefficients and high item-total score correlations. The questionnaire will include the following measures:

☐ **Demographics** -- Items assessing respondents' age, ethnicity, marital status, education, and income. These items have been associated with differences in health outcomes and will be

used as control variables in our multivariate models. They may also be used in interaction terms, or as moderators when applicable.

- ❑ **Symptoms of Distress** – A 15-item scale developed by Orioli et al. (1991) and used in multiple studies by our team (Cook, et al., 2003; Billings et al., 2008). Four items assessing the behavioral signs of stress (e.g., overeating, criticizing others) were summed with four other items assessing the physical signs of stress (e.g., muscle tension, headache). A recent randomized trial (Billings et al., 2008) generated an Alpha of .069. Evidence of validity was generated from Cook et al. (2003) and Billings et al. (2008) where the measure showed significant decreases in subjects exposed to stress management interventions.
- ❑ **Coping With Stress** – A 12-items scale assessing the type of strategies one uses to cope with difficult situations and events. Two subscales are imbedded in the survey – adaptability and situation mastery. Adaptability measures flexibility in coping strategies and situation mastery measures the ability to recognize when and how to appropriately react to stressors. Questions are answered on a 4 point likert scale ranging from never to almost always. Typical questions include: “I often put things aside for a while to get perspective on them”; or “I decide certain problems are not worth worrying about”. (Alpha for the scale was .76 in a previous ISA study).
- ❑ **Nutritional Patterns** – This 12-item scale assesses the nutritional value of the respondent’s diet. It is a modification of the Block Self-Administered Diet History Questionnaire, developed and validated by Block and her associates (Block et al., 1986). The original Block questionnaire was found to correlate 0.70 with more detailed food recall methods, and a later validation study (Block et al., 1990) found that the questionnaire produced group mean nutrient estimates closely approximating the values obtained by three 4-day records. The Nutritional Patterns scale was used by our group in the test of the workplace “Healthy Eating” program with 210 employees of the GMAC insurance company (Cook et al., 2003), in which program participants showed significant improvements in their Nutritional Patterns scores from pretest to posttest ( $F = 77.37$ ,  $p < .001$ ) with an Alpha of 0.64.
- ❑ **Attitudes Toward a Healthy Diet** – This 17-item scale, based on the Health Belief Model, was developed and validated by Trenkner and associates (Trenkner et al., 1990), assesses perceived benefits and barriers to eating a healthy diet. Developed through a sequence of four samples, the administration of the final version to the last sample of 808 respondents yielded an Alpha of .87. The concurrent validity of the scale was demonstrated by significant associations between the scale and other measures of nutrition attitudes and eating behavior. This scale was used as an outcome measure in our test of the “Healthy Eating” program, with program participants showing significant improvements in their scores from pretest to posttest ( $F = 41.04$ ,  $p < .001$ ), and in our RCT of the “Health Connection” program, with program participants showing significant improvements in their scores from pretest to posttest ( $t = 7.67$ ,  $p < .001$ ).
- ❑ **Eating Practices** -- This 10-item subscale is part of the Weight Control Assessment scale developed by O’Neil & Rhodes (in Wolfe, B.L., 1996), and assesses the extent to which the respondent exercises control over their eating. It contains items such as, “How often do eat between meals,” and “Do you have trouble controlling your eating when your favorite foods are around the house?” This subscale was also used in our Healthy Eating field test, with program participants showing significant improvements in their scores from pretest to posttest ( $F = 20.22$ ,  $p < .001$ ), with an Alpha of .63. It was also used in the RCT of our web-based “Health Connection” program (Cook et al., 2007) in which participants showed significant improvements in their Eating Practices scores from pretest to posttest ( $t = 4.72$ ,  $p < .001$ ).

- ❑ **Overeating Self-Efficacy Scale** – A 14-item scale assessing one's confidence in resisting overeating in different situations. Developed by McCann et al. (1995), this scale is a shortened version of the 25-item Eating Self-Efficacy Scale (Glynn & Ruderman, 1986). Glynn and Ruderman (1986) reported an Alpha of .92 and a test-retest reliability of .70 over a 7-week period (N= 484), along with evidence of convergent validity (e.g., ESES scores significantly correlated with dieting behavior).
- ❑ **Diet Behavioral Change Self-Efficacy** – A 5-item scale assessing perceived self-efficacy to engage in more healthful eating practices over the next month. Questions are answered on a 5 point Likert scale ranging from 'Not Confident' to 'Extremely Confident'. Typical questions on this scale include: "How confident are you that you have the skills to eat a healthy diet?"; Or "How confident are you that you have the skills to control the amount or portion size of food that you eat at each meal?". This survey has been used in other ISA studies (Alpha .83).
- ❑ **Height and Weight** – Two items will ask the respondent will be asked to report their height and weight. We do not anticipate checking the validity of that response with actually height and weight measurements.
- ❑ **Exercise Habits** – The Godin Leisure-Time Exercise Questionnaire (Godin and Shephard, 1997) is a brief four-item query of usual leisure-time exercise habits. The first three items ask the respondent to indicate the times per week they engage in strenuous, moderate, and light activities. The fourth item asks how often in a typical 7-day period the respondent engages in activity long enough to work up a sweat. Reliability and concurrent validity of the measure demonstrated by Godin and Shephard (1997). Also used in our RCT of the "Health Connection" (Cook et al., 2007).
- ❑ **Overcoming Barriers to Exercise Self-Efficacy and Self Efficacy to Engage in Regular Exercise** – Two separate measures will assess Self Efficacy for Overcoming Barriers to Exercise and Self Efficacy to Engage in Regular Exercise. The Overcoming Barriers Self Efficacy measure is a 13-item measure developed and validated by McAuley and colleagues (McAuley et al., 1990; McAuley, 1992) asking users to rate on a scale from 0-100 the percentage of confidence they have to exercise in a variety of situations that might be considered barriers to activity. Alpha for this measure was .88. The second measure, an 8-item scale assessing one's confidence in being able to engage in regular exercise. This measure was developed by Kroll et al. and is answered on a 4 point Likert scale ranging from 'Not at All True' to 'Always True'. Typical questions on this scale include: "I can overcome barriers and challenges with regard to physical activity and exercise if I try hard enough"; and "I can accomplish the physical activity and exercise goals that I set". (Alpha = .89).
- ❑ **Planning Physical Activity** – A 2-item measure adapted from Soureti, Schwarzer, and Renner assessing the extent to which the participant has a plan for engaging in physical activity.
- ❑ **Planning Healthy Eating** – Similar to the planning for physical activity, this 2-item measure is also adapted from Soureti, Schwarzer, and Renner and assesses the extent to which the participant has developed a plan for eating a healthy diet.
- ❑ **Tobacco Use** -- Originally used in a study of a workplace smoking cessation program (Jeffery et al., 1993) and adapted by our team in a test of a workplace substance abuse prevention program (Cook et al., 2004), will assess one's use of tobacco. Items include, 1) whether the person smokes cigarettes or uses other tobacco products, 2) the number of days in the past 30 days the person smoked a cigarette or used a tobacco product; 3) the typical number of cigarettes smoked or times tobacco used per day in the past 30 days, 4) whether the person has ever tried to quit, 5) whether the person would like to quit, and 6) number of quit attempts in the past year.

- ❑ **Alcohol use quantity/frequency.** A widely used measure of alcohol consumption, consisting of four items (not a summated scale) that assess: 1) Whether the respondent had a drink in the past 30 days; (2) the number of days in the past 30 days the subject had a drink, 3) the number of drinks usually drunk on those days, and (4) the number of days the subject had five or more drinks at one time. Used in numerous studies of alcohol use in the workplace, including several of our studies (e.g., Cook et al., 1996b; Cook et al., 2004; Deitz et al., 2005).
- ❑ **Belief About Aging** – This 5-item measure, developed by the study team will assess participants beliefs about aging.

(C) a brief description of the analyses that will be performed on the biologic or non-biologic (i.e. questionnaires) samples collected

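### Two of the six tobacco items, on quit attempts, look back further than the three-month follow-up; if reused unchanged at posttest, one gains avoidable noise and the other is insensitive by construction

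*Protocol*

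**What the plan says.** The Tobacco Use entry under Outcome Measures (Protocol, item 16, part B) lists six items:

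- Item 1, current status: "whether the person smokes cigarettes or uses other tobacco products".
- Item 2, 30-day window: "the number of days in the past 30 days the person smoked a cigarette or used a tobacco product".
- Item 3, 30-day window: "the typical number of cigarettes smoked or times tobacco used per day in the past 30 days".
- Item 4, lifetime window: "whether the person has ever tried to quit".
- Item 5, current wish: "whether the person would like to quit".
- Item 6, 12-month window: "number of quit attempts in the past year".

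The Narrative (part A) places randomization after the pretest. The experimental arm uses the program "over multiple sessions during the three-month administration period", and all participants then receive the posttest. Of the posttest it says: "That data collection will be conducted in a manner similar to the pretest".

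The section on analysis of primary outcomes (part C) counts tobacco use among the primary outcome domains but does not say which of the six items is the endpoint. The analysis is an ANCOVA of the posttest value, adjusted for the baseline value of the same variable and tested two-sided at 5%.

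**The concern.** A posttest measure should mainly reflect behavior after randomization. Items 4 and 6 do not, because their look-back is longer than the follow-up. At a three-month posttest, most of what a participant reports on item 6, and nearly all of what counts toward item 4, happened before the arms were formed.

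Those earlier attempts carry no information about the program. At stake is how well the trial can detect an effect on quit attempts, a plausible early response to a three-month program. Only tobacco users contribute to this comparison, so the effective sample may be small and precision is worth protecting. Question wording has to be settled before the posttest is collected; no later analysis can restore a window that was not asked about.

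**Working it through.** The protocol gives no tobacco prevalence, quit-attempt rate, effect size or power for this outcome, so there is no figure to reproduce.

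**Inputs from the protocol.** Posttest at about 3 months; recall of 12 months (item 6) and lifetime (item 4); 150 per arm; loss of at most 20%, leaving 150 × 0.8 = 120 per arm; two-sided 5% test; ANCOVA on the baseline value.

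**Assumed inputs.** Tobacco use in 10–20% of participants (12–24 users per arm of 120); 1–2 quit attempts per user per year, Poisson; rate multiplied by 1.5–2 during the three program months in the experimental arm; analysis among users; same wording at both surveys.

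**1. Share of each window before randomization.**
- Item 6: (12 − 3)/12 = 75%.
- Item 4: nearly all of a lifetime.
- Items 2 and 3: 0%, since 30 days lie inside the three months.
- Items 1 and 5: no look-back.

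**2. Item 6, expected difference** (2 attempts a year, doubled rate).
- Control: 1.5 (nine earlier months) + 0.5 = 2.0.
- Experimental: 1.5 + 1.0 = 2.5.
- Difference: 0.50. With a three-month window it is 1.0 − 0.5 = 0.50, the same.

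**3. Item 6, variance.** The pretest covers months −12 to 0 and the posttest months −9 to +3, so nine months are shared.
- Past-year item, unadjusted: (2.0 + 2.5)/2 = 2.25.
- Past-year item, ANCOVA: 2.25 − 1.5²/2.0 = 1.125.
- Three-month item: (0.5 + 1.0)/2 = 0.75.

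Baseline adjustment halves the variance, but 1.125 is still 1.5 times 0.75.

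**4. Item 6, power with 24 users per arm.** SE = √(2 × variance/24); power ≈ Φ(0.50/SE − 1.96).
- Past-year, unadjusted: SE 0.433, power 21%.
- Past-year, ANCOVA: SE 0.306, power 37%.
- Three-month: SE 0.250, power 52%.

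Simulation of the planned ANCOVA (3,000 replicates) gave 37% for the past-year item and 50% for the three-month item. With gamma variation in rates between persons it gave 28% and 38%.

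The same formulas over the range of assumptions, with ANCOVA throughout:

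| Users per arm | Attempts/year | Rate ratio | Past-year item | Three-month item |
|---|---|---|---|---|
| 12 | 2 | 2 | 21% | 29% |
| 24 | 1 | 2 | 21% | 29% |
| 24 | 2 | 1.5 | 14% | 19% |
| 24 | 2 | 2 | 37% | 52% |
| 120 (every completer a user, for contrast) | 2 | 2 | 95% | 99% |

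**5. Item 4.** Let p be the share who had already tried to quit at pretest (assumed 60–80%), and suppose 10% of control and 20% of experimental users attempt during the program, whatever their history. The posttest share answering yes is p + (1 − p) × attempt rate.
- p = 0.6: 0.64 against 0.68, a difference of 4 points.
- p = 0.8: 0.82 against 0.84, a difference of 2 points.
- A question about the last three months would show 10 points.

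The difference is multiplied by (1 − p). Baseline adjustment cannot restore it, because those who said yes at pretest have no room to move.

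**The case against.** The strongest case against has four parts.

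- **The measure of tobacco use itself is sound.** Items 1 to 3 capture current use and consumption, with no look-back or one wholly inside the follow-up. Items 4 and 6 concern quit history, and the protocol names neither as the endpoint. This stands. A reader might infer that the primary tobacco outcome is diluted; the protocol does not support that.
- **The planned contrast on item 6 is not shrunk.** A reader might reason that a doubled rate shows up as only (9 + 3 × 2)/12 = 1.25 over a year and treat that as the loss. But the protocol tests an adjusted difference in means, which keeps its expected size. Only precision suffers, and the ANCOVA recovers part of it. This stands for item 6 but not for item 4.
- **The number of users limits power more than the window does.** With few users, power is low under either wording. A reader might infer that the long window will cause a real effect to be read as absent; without a stated prevalence or attempt rate, that cannot be claimed. The avoidable loss remains, but it is one contributor among others.
- **Reuse of the wording is an inference.** The draft questionnaire is not shown, and the sentence on a similar manner describes how data are collected, not necessarily the question stems. Adjustment for the baseline value of the same variable makes reuse likely, but it cannot be confirmed.

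Keeping items from earlier workplace studies is also a defensible reason for the current wording. It does not require the same look-back at posttest.

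**Conclusion.** The point holds in a limited form and is of minor importance. Two of six tobacco items have recall windows that suit a pretest but not a three-month posttest. For the past-year count the cost is precision: residual variance about 1.5 times that of a three-month item after baseline adjustment, or power of about 37% against 50% in the main assumed case. For the lifetime item the difference itself falls, from 10 points to between 2 and 4 under the assumed range.

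The window arithmetic for item 6 (75%) follows from the protocol, provided the wording is reused. The power figures and the item 4 figures rest on assumed prevalence, attempt rates, rate ratios and quit history, and only illustrate the size. Nothing here bears on the 30-day or current-use items.

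**What to change.** On the posttest only, replace items 4 and 6 with two questions covering the period *since you completed the first survey (about three months ago)*: whether any quit attempt was made, and how many. Keep the lifetime and past-year items at pretest as descriptors, and use the pretest past-year count as the baseline covariate for the posttest count.

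The cost is two reworded questions. The covariate is then no longer the identical item, so the primary-analysis paragraph needs one added line stating that, for quit attempts, the adjustment uses the pretest past-year count. ANCOVA does not require the baseline and posttest measures to be the same.
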